## 4 ANALYSIS SETS/ POPULATIONS/SUBGROUPS

The analysis set consists of all 67 participants across all sites. Liver disease progression as measured using Fibroscan is defined as an increase in Fibroscan Stage (F1≤5.8 kPa (kiloPascals), F2 5.9-7.5 kPa, F3 7.6-9.3 kPa, F4>9.4 kPa) from baseline result to last study time point (either 36 months or last completed data point). These patients are referred to as “**progressors**”. Patients in the study are expected to show either no change, regression (decrease in Fibroscan Stage), or progression. Patients who do not show progression are referred to as “**non-progressors**”. Some participants’ fibrosis stage may fluctuate between first and last Fibroscan, such cases will be described but status will be defined only on first and last Fibroscan result. In addition, a pre-determined secondary definition of fibrosis progression was added, defined as 20% increase and ≥2 kPa (at least one value >5.9 kPa) [3].

Key subgroups of interest based on study entry characteristics include:

- HBeAg status at baseline (positive vs negative)
- Nadir CD4 cell count at baseline (>200 vs ≤200)
- CD4 nadir (%) (<10 or ≥10%)
- HIV viral load at CD4 nadir at baseline (>200,000 vs ≤ 200,000)
- ART duration (≤10 or >10 years)
- Derangement of ALT from normal range (yes vs no) – cut-offs are gender and site specific

Other exploratory subgroups (depending on numbers in each subgroup): gender (male vs female) and site (Bangkok vs others).

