## 5 ENDPOINTS AND COVARIATES

**Table 2 Endpoints and covariates**

| Grouping                                                                                        | Variable                                                                                              | Comment                                                                          |
|-------------------------------------------------------------------------------------------------|-------------------------------------------------------------------------------------------------------|----------------------------------------------------------------------------------|
| Endpoints (measured repeatedly over time)                                                |                                                                                                       |                                                                                  |
| Microbial translocation/
immune activation
Collected 6-monthly (7)
analysed yearly (4) | sCD14 (pg/mL)
CXCL10 (pg/mL)                                                                       | Continuous
Continuous                                                         |
| Hepatic Inflammation
Collected 6-monthly (7)
analysed yearly (4)                          | ALT (IU/L)
AST (IU/L)
Albumin (g/L)                                                             | Continuous
Continuous
Continuous                                           |
| Liver disease severity
Collected yearly (4)                                                  | Fibrosis (kPa)                                                                                        | Continuous                                                                       |
| Liver disease progression
One value (1)                                                      | Progression (Grade change) (yes/no) (primary)
Progression (kPa change) (yes/no) (secondary)        | Binary
Binary                                                                 |
| Markers of cell death
Collected 6-monthly (7)
analysed yearly (4)                         | HMGB1 (ng/mL)                                                                                         | Continuous                                                                       |

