Correlations within and between endpoints at each visit and change from baseline visit will be explored (e.g., correlation sCD14 and Fibroscan score at month 12) and between consecutive follow-up visits and change from baseline visit separately (e.g., correlation sCD14 at month 12 with Fibroscan score at month 24). The Spearman correlation, exploring the degree to which the relationship between two outcomes is monotonic, will be used between two continuous outcomes and between an ordinal and continuous outcome, and point-biserial correlation between a binary and continuous outcome.

The following univariate models will be fitted to estimate the association between with the known risk factors (covariates) listed in Table 2 with each endpoint separately, both univariable (one covariate - unadjusted) and multivariable (more than one covariate - adjusted):

1. Univariate logistic regression model with the binary outcome of liver disease progression during the study (yes/no) adjusted for CD4+ T-cells at study entry (except for variables related to CD4).
2. Univariate mixed regression model with each outcome the repeated continuous outcome in microbial translocation/immune activation, hepatic inflammation, and Fibroscan score (kPa) adjusted for CD4+ T-cells at study entry (except for variables related to CD4).

In model 2 the functional form of time in the model will be explored (i.e., linear or curvilinear [e.g., quadratic, cubic]), a random intercept will be included in these models to represent a random effect for subject and the structure of the residual (within-patient) variance-covariance matrix will explored (e.g., unstructured, AR(1),...).

We will examine longitudinal liver stiffness measured by Fibroscan as a continuous variable in kPa and compare between those classified as progressors and non-progressors via univariate mixed regression.

### 7.1.2 Aim 2

Longitudinal plots by subgroup will be created of the microbial translocation/immune activation outcomes, hepatic inflammation outcomes, and liver disease outcomes. We will start by exploring subgroups in the univariate models outlined in Aim 1 by including appropriate interaction terms. It should be noted that the sample size will be a limiting factor in detecting statistically significant subgroup differences.

Analyses will be conducted using STATA, SPSS, or SAS.

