## 9 SAMPLE SIZE

Participants were recruited as part of a larger multi-centre cross sectional and longitudinal cohort which had multiple aims related to liver disease pathogenesis in HIV-HBV co-infection and HIV persistence in the liver. The sample size paragraph below relates to the larger cohort (n=100) that was planned in a previous grant

**Planned sample size:** Persons who experience liver disease progression during the follow-up period are expected to have an increase in liver stiffness (kPa) over time. Based on a recent retrospective study of liver stiffness using only 2 fibroscan measures in 92 HIV-HBV co-infected patients we expect that at least 8% of patients will have evidence of increased liver stiffness on HAART. Assuming the same distribution of LPS as described in grant APP 1024406, a sample of 100 patients will have 80% power at the 5% significance level to detect a minimum odds ratio of liver disease progression of 2.8 in patients with LPS in the upper quartile compared to the lower quartile.

**Actual sample size:** A sample of 67 patients will have less than 80% power at the 5% significance level to detect a minimum odds ratio of liver disease progression of 2.8 in patients with LPS in the upper quartile compared to the lower quartile.

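### Both progression outcomes are yes/no cuts of kPa and no planned model tests a marker against kPa change; a continuous progression analysis should be added

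*SAP*

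**What the plan says.** Section 4 defines progression as a rise in Fibroscan stage between the first and last scan, with bands F1 up to 5.8 kPa, F2 5.9-7.5, F3 7.6-9.3 and F4 above 9.4. Intermediate scans do not affect status. "Patients who do not show progression are referred to as" non-progressors, so stable and improving patients form one group. The secondary definition is a rise of 20% and at least 2 kPa with one value above 5.9 kPa, which is again yes/no. Table 2 lists the stage version as "Progression (Grade change) (yes/no) (primary)".

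Table 2 also lists fibrosis in kPa as a continuous endpoint collected at four visits.

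Section 7.1.1 uses these outcomes in four ways:
- Model 1 is a "Univariate logistic regression model with the binary outcome of liver disease progression during the study (yes/no) adjusted for CD4+ T-cells at study entry".
- Model 2 is a mixed model for each repeated continuous outcome, including kPa. It has a random intercept, a form of time to be explored, and the same CD4 adjustment.
- kPa over time is compared between progressors and non-progressors.
- Rank correlations, including on change from baseline, are to be explored.

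Section 9 states that "we expect that at least 8% of patients will have evidence of increased liver stiffness on HAART" and that 67 patients give less than 80% power.

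**The concern.** Aim 1 asks whether markers predict progression, which is a change in stiffness. The outcomes that carry that name reduce two kPa readings to one bit, and whether a patient counts depends partly on how close the first reading lies to a band edge. The analysis that keeps kPa continuous is not written as an analysis of change. With 67 patients and about 5 expected progressors at the 8% in Section 9 (0.08 × 67 = 5.4), a null result from model 1 would say little. The same scans could answer the question better, but no planned model is set up to do so.

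**Working it through.** **1. How the two definitions classify the same movement** (Section 4).

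| First → last scan | Change | Primary (stage) | Secondary |
|---|---|---|---|
| 5.8 → 5.9 kPa | 0.1/5.8 = +1.7% | F1 to F2: progressor | No |
| 5.9 → 7.5 kPa | 1.6/5.9 = +27% | F2 to F2: non-progressor | No (under 2 kPa) |
| Starts in F4, any rise | any | Never a progressor | Possible |

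**2. What model 2 tests.** For Aim 1, Section 7.1.1 specifies a covariate, time, a random intercept and CD4 at entry. Without a covariate-by-time term, the covariate coefficient is a difference in average kPa over all visits. Baseline kPa is not a stated adjustment. Table 2 lists baseline stage as a covariate, but only as categories. Interaction terms appear only in Section 7.1.2, for subgroups. The comparison of kPa between progressors and non-progressors cannot fill the gap, because kPa defines the groups.

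**3. The plan's own power figure** (Section 9: "a sample of 100 patients will have 80% power at the 5% significance level"; the effect is an odds ratio of 2.8, with 8% progressors; two-sided test assumed). The logistic formula for a continuous covariate is N = (1.960 + 0.842)² / [P(1−P)b²]. With P = 0.08 and b = ln 2.8 = 1.030 per SD, N = 7.849 / (0.0736 × 1.060) = 101, and power at n = 100 is 79.8%. The same formula gives 62.8% at n = 67, consistent with the SAP's less than 80%. The match needs the odds ratio to be per SD. A literal comparison of outer quartiles (25 v 25 patients, 8% v 19.6%) gives 22% at n = 100 and 16% at n = 67. The marker distribution behind the figure is in a grant that is not shown ("Assuming the same distribution of LPS as described in grant APP 1024406"), and Section 13 records that LPS was later removed as an outcome. No stated power therefore applies to the current markers.

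**4. Cost of the cut, normal theory.** The efficiency of a cut outcome relative to the uncut normal outcome is ARE = φ(c)² / [P(1−P)], with c = Φ⁻¹(1−P). If the continuous analysis has 80% power, the binary one has Φ(2.802√ARE − 1.960). At P = 0.08, c = 1.405 and φ(c) = 0.1487, so ARE = 0.0221/0.0736 = 0.30 and power = Φ(1.535 − 1.960) = 34%.

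| Progressors | ARE | Effective n of 67 | Power left from 80% |
|---|---|---|---|
| 8% | 0.30 | 20 | 34% |
| 15% | 0.43 | 29 | 45% |
| 25% | 0.54 | 36 | 54% |
| 50% (best case) | 0.64 | 43 | 61% |

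**5. Simulation with the SAP's own bands**, n = 67. All kPa inputs are assumptions: baseline median 5.5-6.5 kPa, log SD 0.30-0.45, three-year log change with mean −0.1 to 0 and SD 0.15-0.25. Where kPa change had 70-78% power, stage increase had 16-45%. For example, with median 6.5, log SD 0.45, mean change 0, change SD 0.25 and marker-change correlation 0.34, 19.5% progress. Power is then 33% for stage increase, 70% for kPa change and 79% for log-kPa change.

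**6. A model kinder to the binary outcome.** Suppose the marker predicts membership of a true progressor class (8-25% of patients), which gains 0.4 log kPa, with scan error of 0.10-0.15 log units. Baseline-adjusted log kPa still has more power, but by less. At an odds ratio of 2.8 per SD the comparison runs from 17% v 29% to 44% v 67%. At 1.5 per SD both can be near 7-8%.

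**The case against.** The strongest reply is that the continuous information is not lost. kPa is its own endpoint group in Table 2, model 2 analyses it, and Aim 1 covers severity as well as progression. The word primary may only rank two definitions within one row: Section 4 calls the other a secondary definition, and nothing says that the answer to Aim 1 rests on either. This stands. A reader might infer that the SAP discards continuous kPa, or has one formal primary endpoint on which everything depends; the document supports neither. It does not remove the gap, because model 2 as written does not address change. The correlations on change from baseline are exploratory and unadjusted, and Section 13 records that none were obtained.

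A reader might also infer that the binary outcome halves the power. The SAP gives no kPa SD, repeatability or marker effect, so no single figure follows from it. A halving fits roughly 15-25% progressors under a smooth marker effect. The loss is larger at 8%, and smaller under the progressor-class model or with a strong effect and many progressors (91% v 99% in a latent-logistic simulation with 25% progressing and an odds ratio of 2.8 per SD). The 8% itself is a lower bound from another cohort and is not a rate of stage increase.

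Nor is pooling regression with no change the main fault. It follows from asking about progression, and in the band simulation at correlation 0.34 a three-level score recovered only about 2-14 points.

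Finally, Section 13 describes models as already fitted, so replacing the primary label now would look like outcome switching. That is a sound objection to relabelling, but not to a declared addition. The rationale for the stage cut may sit in the protocol, so its absence from the SAP is not held against the plan.

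**Conclusion.** The point holds in this form: progression is defined only by two yes/no cuts of first-to-last kPa, the primary one behaves erratically at band edges and cannot register worsening from F4, and no planned model is specified to test a marker against kPa change. The classification and the missing model terms follow from the SAP text alone. The size of the power loss does not. It is about 26 to 46 points from 80% under normal theory with 25% down to 8% progressors (80 − 54 and 80 − 34), and from about 1 to 23 points if the marker acts only through a progressor class. The continuous analysis had more power in every scenario examined. This is worth changing, but it does not invalidate the planned analyses.

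**What to change.** In Section 7.1.1, add one continuous progression analysis for Aim 1, in either form:
- regress last-scan log kPa on the marker, with baseline log kPa as covariate and the existing CD4 adjustment; or
- fit the log-kPa mixed model over the four scans with a marker-by-time term, and read the result from that term.

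Name the marker as the explanatory variable, since Section 7.1.1 describes the models as relating Table 2 covariates to endpoints and Table 2 files the markers under endpoints. Report the result beside the stage-increase result as the main evidence on association with progression. Keep both binary definitions as clinically readable summaries. Record the addition in Section 13 as a dated amendment, stating that models had already been fitted, and leave the existing primary label in place.

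The cost is a paragraph of SAP text and one regression per marker on data already collected. The effect is a ratio of kPa, less familiar to clinicians than a stage change, and the analysis must carry the label of a late addition.

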## 6 HANDLING OF MISSING VALUES AND OTHER DATA CONVENTIONS

Summary statistics (e.g., percentages) will be based on non-missing values. When applying the mixed model regression model, the underlying assumption on missing data is missingness at most at random.

## 7 STATISTICAL METHODOLOGY

### 7.1 STATISTICAL PROCEDURES

A study flow-chart will be created to depict the flow of study participants over time based on the available data of the key outcome (i.e., liver disease).

Key baseline parameters will be summarised to describe the study cohort underlying all analyses. Using the variables presented in this table, we will explore whether progressors and non-progressors differ in any of the key variables at baseline.

We will test for differences between progressors and non-progressors using the wilcoxon rank-sum test for continuous data and the chi-square test or Fisher's exact test for categorical data. These key baseline parameters will also be summarised by subgroup (see Section 4) to explore for differences, using tests similar to those described for progressors/non-progressors. Continuous data will be presented as median with 25th - 75th percentile if data are considered skewed. Categorical data will be presented as frequency and percentages (based on non-missing data points).

### 7.1.1 Aim 1

Summaries will be presented of all endpoints (microbial translocation/immune activation outcomes, hepatic inflammation outcomes, and liver disease outcomes) listed in Table 2 at baseline and each follow-up time point and change from baseline to each follow-up time point. These summaries will also be created separately for those who are progressors or non-progressors. If the endpoint requires transformation (e.g., log transformation in case of positively skewed data) before fitting of a model (see below), summaries will also be presented on the transformed scale.

Longitudinal plots will be created of the endpoints, depicting more than one endpoint together in a graph to visually explore trends over time within and between endpoints, presented both by visit and change from baseline to each follow-up visit. These graphs will also be created separately for those who are progressors or non-progressors. If the endpoint requires transformation (e.g., log transformation in case of positively skewed data) before fitting of a model (see below), plots will also be presented on the transformed scale.

Correlations within and between endpoints at each visit and change from baseline visit will be explored (e.g., correlation sCD14 and Fibroscan score at month 12) and between consecutive follow-up visits and change from baseline visit separately (e.g., correlation sCD14 at month 12 with Fibroscan score at month 24). The Spearman correlation, exploring the degree to which the relationship between two outcomes is monotonic, will be used between two continuous outcomes and between an ordinal and continuous outcome, and point-biserial correlation between a binary and continuous outcome.

The following univariate models will be fitted to estimate the association between with the known risk factors (covariates) listed in Table 2 with each endpoint separately, both univariable (one covariate - unadjusted) and multivariable (more than one covariate - adjusted):

1. Univariate logistic regression model with the binary outcome of liver disease progression during the study (yes/no) adjusted for CD4+ T-cells at study entry (except for variables related to CD4).
2. Univariate mixed regression model with each outcome the repeated continuous outcome in microbial translocation/immune activation, hepatic inflammation, and Fibroscan score (kPa) adjusted for CD4+ T-cells at study entry (except for variables related to CD4).

In model 2 the functional form of time in the model will be explored (i.e., linear or curvilinear [e.g., quadratic, cubic]), a random intercept will be included in these models to represent a random effect for subject and the structure of the residual (within-patient) variance-covariance matrix will explored (e.g., unstructured, AR(1),...).

We will examine longitudinal liver stiffness measured by Fibroscan as a continuous variable in kPa and compare between those classified as progressors and non-progressors via univariate mixed regression.

### 7.1.2 Aim 2

Longitudinal plots by subgroup will be created of the microbial translocation/immune activation outcomes, hepatic inflammation outcomes, and liver disease outcomes. We will start by exploring subgroups in the univariate models outlined in Aim 1 by including appropriate interaction terms. It should be noted that the sample size will be a limiting factor in detecting statistically significant subgroup differences.

Analyses will be conducted using STATA, SPSS, or SAS.

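### Model 1 is a logistic regression on possibly few progressors with no small-sample estimator named; Firth's penalised likelihood, without subgroup interactions in that model, would be a cheap improvement

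*SAP*

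**What the plan says.** Section 7.1.1 lists two models for relating the Table 2 covariates to the endpoints, each fitted unadjusted and adjusted. The first is a "Univariate logistic regression model with the binary outcome of liver disease progression during the study (yes/no) adjusted for CD4+ T-cells at study entry", with the CD4 term left out when the covariate is itself a CD4 variable. Many Table 2 covariates are binary. The second is a mixed model for the repeated continuous outcomes, including liver stiffness in kPa.

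For Aim 2, section 7.1.2 says: "We will start by exploring subgroups in the univariate models outlined in Aim 1 by including appropriate interaction terms". The Aim 1 models include the logistic one.

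On numbers, section 4 says "The analysis set consists of all 67 participants across all sites", and section 9 says "we expect that at least 8% of patients will have evidence of increased liver stiffness on HAART". That rate comes from "a recent retrospective study of liver stiffness using only 2 fibroscan measures in 92 HIV-HBV co-infected patients". The primary event here is different: section 4 has progression "defined as an increase in Fibroscan Stage" between first and last scan.

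No exact or penalised method is named for the regression; Fisher's exact test appears in section 7.1 only for the descriptive group comparisons. Section 8 plans no sensitivity analyses. Section 7.2 has associations interpreted by magnitude and direction, in addition to p-values and 95% confidence intervals.

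**The concern.** A logistic regression named without an estimator will be run by maximum likelihood, the usual software default. With few events, maximum likelihood pushes non-null odds ratios away from 1. If every progressor, or none, falls in one level of a binary covariate, the estimate is infinite and the Wald interval is useless. Magnitude is one of the things section 7.2 asks readers to weigh, so the bias bears on interpretation. The SAP's caveat in section 7.1.2 is about detecting significant subgroup differences; it warns of low power, not of exaggerated or infinite estimates.

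Interaction terms make this worse, because they divide the same few events among more cells. They also fit Aim 2 poorly in Model 1. Each patient contributes one yes/no outcome, so whether subgroups differ in progression is the subgroup main effect. A subgroup-by-covariate interaction there answers a different question.

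**Working it through.** **Inputs.** N = 67 (section 4); event rate at least 8%, planned N = 100, 80% power, 5% level, odds ratio 2.8 for upper versus lower LPS quartile (section 9); site split 31 vs 36 (Table 1). Assumed, because the SAP does not give them: event rates above 8%, effect per SD, normal covariates, and carrier counts for binary covariates other than site.

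**The plan's own figure.** Section 9 states that "a sample of 100 patients will have 80% power at the 5% significance level". For a continuous covariate, two-sided:

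n = (1.960 + 0.842)² / [p(1 − p)(ln OR)²] = 7.849 / [0.08 × 0.92 × (ln 2.8)²] = 100.6.

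This agrees with 100, but only if the quartile contrast is taken as one SD. The same formula gives 63% power at 67, consistent with the SAP's statement that power is below 80%. If 2.8 is instead the contrast between the medians of the outer quartiles of a normal covariate (about 2.30 SD apart), the odds ratio per SD is 2.8^(1/2.30) ≈ 1.56. Both readings are carried below; the smaller was simulated at 1.57.

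**Event count.** 67 × 0.08 = 5.4. At exactly 8%, the binomial chance of fewer than 10 events is 96%. Since 8% is a floor: 15% gives about 10 events, 20% about 13, 30% about 20.

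**Bias for a continuous covariate.** Simulation at N = 67 with one further continuous adjuster in the model, 2,000 runs per row. Values are geometric mean odds ratios; maximum likelihood (ML) over finite fits only.

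| True OR per SD | Event rate | ML | Firth | SD of log OR, ML / Firth |
|---|---|---|---|---|
| 2.8 | 8% | 3.35 | 2.71 | 0.82 / 0.59 |
| 2.8 | 15% | 3.20 | 2.80 | 0.52 / 0.44 |
| 2.8 | 30% | 3.10 | 2.82 | 0.41 / 0.37 |
| 1.57 | 8% | 1.71 | 1.57 | 0.67 / 0.54 |
| 1.57 | 30% | 1.64 | 1.58 | 0.32 / 0.30 |
| 1.0 | 8% | 0.99 | 0.99 | 0.61 / 0.50 |

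Repeat simulations of the first row gave 3.44 to 3.49 by ML and 2.78 to 2.82 by Firth. About 1% of ML fits in that row were infinite.

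**Empty cells for a binary covariate with no true effect.** With d events and k carriers, P(zero cell) = [C(67 − k, d) + C(k, d)] / C(67, d). For site with 5 events: (376,992 + 169,911) / 9,657,648 = 5.7%.

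| Carriers of 67 | 5 events | 10 events |
|---|---|---|
| 31 (site, Table 1) | 5.7% | 0.1% |
| 20 (assumed) | 16% | 2% |
| 13 (assumed) | 33% | 10% |
| 8 (assumed) | 52% | 25% |

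**Interactions in Model 1** (true interaction odds ratio 2.8 assumed, 1,500 runs). At 8% events, a continuous-by-binary interaction was infinite in 26% of ML fits and averaged 4.22 in the rest; a binary-by-binary one was infinite in 76%. At 30% events the infinite shares were 1% and 8%. Firth gave 2.37 and 2.16 at 8%, with SDs of the log odds ratio of 1.1 and 1.6. At 20% to 30% it centred near 2.8 to 2.9, but the SD was still 0.9 to 1.4.

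**The case against.** Several points on the other side stand.

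- A reader might infer that about five progressors are expected. The SAP does not say so. Its 8% is a minimum, for increased stiffness in an earlier two-scan study, in a paragraph that section 9 assigns to the larger planned cohort of 100. The primary event is any rise in stage, and the F2 and F3 bands span only 1.6 and 1.7 kPa, so more events are plausible.
- The 2.8 is an LPS quartile contrast, and section 13 records that LPS was dropped as an outcome. Using 2.8 per SD is an assumption at the upper end. At 1.57 the inflation is small, with no true effect there is none, and the median ML estimate at 2.8 and 8% events is only about 3.0.
- A reader might infer that infinite odds ratios will be common. That depends on carrier counts the SAP does not report; for site, the one split it gives, the chance is low. Section 13 also shows subgroups being revised to manage low numbers.
- Fisher's exact test in the descriptive comparisons remains valid with a zero cell, so a sparse covariate would not vanish from the report.
- Section 7.2 does not make magnitude the sole basis for interpretation.
- The wording on appropriate interaction terms does not prescribe any particular interaction in Model 1, and already allows subgroup-by-time in the kPa mixed model.

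None of this supplies an estimator for sparse data. Firth had the smaller spread at every event rate tried for a continuous covariate, and stayed close to the true value. The gap is real, though its size depends on a count the SAP does not give.

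**Conclusion.** The point holds as a modest improvement to an exploratory analysis. Model 1 names no small-sample estimator, and the SAP's only rate allows as few as about 5 progressors in 67. For a continuous covariate with assumed odds ratio 2.8 per SD, ML overstates the odds ratio by roughly 20% to 25% at 8% events (3.35 to 3.49 against 2.8) and 11% at 30% (3.10 / 2.8); at 1.57 the figures are about 9% and 4%. Infinite estimates are a real risk only for uncommon binary covariates or low event counts. That ML would be used is inferred from the default, as the SAP does not name it.

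A reader might also infer that penalisation rescues the interactions. It makes them finite, but at 8% events they are biased low and at every rate they are very imprecise. The Aim 2 part therefore reduces to keeping subgroup interactions out of Model 1 and saying which interaction is meant.

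**What to change.** In section 7.1.1, state that Model 1 is fitted by Firth-penalised logistic regression with profile-likelihood confidence intervals, for both the primary and the secondary definition of progression. In section 7.1.2, state that the Aim 2 interaction is subgroup-by-time in the mixed model for continuous kPa, that no subgroup interactions are fitted in Model 1, and that progression by subgroup is reported as counts with exact intervals.

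The cost is a line or two of text. Firth's method is available for Stata and SAS, two of the three packages the SAP names. Section 13 speaks of adjusted models as already fitted; if so, the cost includes refitting them. The statistical downside is slight shrinkage toward 1, and if progressors prove numerous the results will differ little from maximum likelihood.
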